#### Data analysis

Patient-level data will be clustered by site and clinician. Patients will be assigned to a single phase based on the date of their first encounter with a clinician at the site during the project period. Instances in which a patient has a repeated visit in the pre- and active implementation periods will be recorded to enable sensitivity analyses accounting for repeated observations.

Regression analyses will compare quantitative outcome measures (including survey scores and Option Grid use) between the pre- and active implementation phases while adjusting for patient and clinician characteristics. The extent to which clinicians involve patients in decision-making for each recorded encounter will be assessed by analyzing the Observer OPTION-5 and Option Grid fidelity checklist data from each phase of the study. We will conduct a framework analysis, guided by NPT, of the clinician interview transcripts to determine the barriers and facilitators of Option Grid implementation. Completion of the NoMAD Normalization Process Theory survey, based on interviews with site stakeholders, will enable us to make across-site assessments of implementation sustainability.

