**Methods:**

We will conduct a randomized stepped-wedge implementation study where five sites will be randomized to implement the uterine fibroid Option Grid PDA in practice at different time points. Implementation will be guided by the Consolidated Framework for Implementation Research (CFIR) and Normalization Process Theory (NPT). There will be a 6-month pre-implementation phase, a 2-month initiation phase where participating clinicians will receive training and be introduced to the Option Grid PDAs (available in text, picture, or online formats), and a 6-month active implementation phase where clinicians will be expected to use the PDAs with patients who are assigned female sex at birth, are at least 18 years of age, speak fluent English or Spanish, and have new or recurrent symptoms of uterine fibroids. We will exclude postmenopausal patients. Our primary outcome measure is the number of eligible patients who receive the Option Grid PDAs. We will use logistic and linear regression analyses to compare binary and continuous quantitative outcome measures (including survey scores and Option Grid use) between the pre- and active implementation phases while adjusting for patient and clinician characteristics.

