### Participants

We will include physicians (attending or resident) who consent to participate in our implementation study and provide care to women with symptomatic uterine fibroids during the project duration at participating sites.

We will include patients showing new or recurrent symptoms of uterine fibroids (e.g., heavy menstrual bleeding, pelvic pressure or pain) who are seeking treatment and meet all of the following inclusion criteria: (i) assigned female sex at birth, (ii) at least 18 years of age, (iii) speak English or Spanish, and (iv) have the ability to complete short surveys online independent of assistance. We will not exclude pregnant patients. We will exclude postmenopausal patients because they may have different treatment options than those presented in the Option Grid PDA used in this study.

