#### Active implementation phase

During each site’s active implementation phase, the uterine fibroid Option Grid PDA will be incorporated into the routine clinic workflow according to a tailored implementation strategy, as described in the “intervention” section above. Each site will keep a weekly record of the number of eligible patients who received the Option Grid (primary outcome).

As in the pre-implementation phase, patients will be asked to complete a survey (1) immediately following the clinical encounter and (2) 3 months after the clinical encounter.

Two months into the active implementation phase, research assistants at each site will begin audio-recording clinical encounters until each participating clinician (who consents to audio-recording) has had five of their encounters recorded. The audio-recordings will be sent to the project team at Dartmouth using a secure and HIPAA-compliant platform (Dartmouth Sharepoint). Two independent raters will assess (using the Observer Option-5 measure and fidelity checklist) the extent to which clinicians involve patients in the decision-making process using Option Grid tools. At the end of the active implementation phase, clinicians will complete the ADOPT survey, and we will conduct semi-structured interviews, guided by CFIR and NPT, with a convenience sample of participating clinicians to determine the tools’ utility, and the barriers and facilitators of their use in practice.

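### Assigning each patient to the phase of her first encounter gives the two phases unequal look-back, so their case mix is likely to differ in a way that tracks phase and can bias the survey comparisons

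*Protocol article*

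**What the plan says.** All references are to the protocol article.

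- **Phase rule (Data analysis).** Patients are "assigned to a single phase based on the date of their first encounter with a clinician at the site during the project period".
- **Phase lengths (Abstract, Methods).** "There will be a 6-month pre-implementation phase, a 2-month initiation phase where participating clinicians will receive training", followed by "a 6-month active implementation phase where clinicians will be expected to use the PDAs".
- **Eligibility (Participants).** "We will include patients showing new or recurrent symptoms of uterine fibroids", provided they are seeking treatment. The same criteria apply in both phases, with no washout and no requirement to be new to the clinic.
- **Comparison (Data analysis).** "Regression analyses will compare quantitative outcome measures (including survey scores and Option Grid use) between the pre- and active implementation phases", adjusted for characteristics of patients and clinicians that are not itemised.
- **Repeat visits (Data analysis).** "Instances in which a patient has a repeated visit in the pre- and active implementation periods will be recorded to enable sensitivity analyses" that account for repeated observations.
- **Counting receipt.** Under Active implementation phase: "Each site will keep a weekly record of the number of eligible patients who received the Option Grid". Under Primary outcome measure, eligible patients come from the outpatient scheduling system. Paper receipt is counted from numbered stubs that carry the clinician's name and grade. Numerator and denominator go into one weekly log. Under Pre-implementation phase, the tool is not used before initiation.

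**The concern.** The rule looks neutral but treats the phases differently. In the first months of the project period almost any visit can be a patient's first, so the pre-implementation group draws on the pool of women already attending the clinic. By the active phase that pool has been used up: anyone seen in the previous 8 months has already been assigned elsewhere.

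New and returning patients may differ in how much remains to be decided, in the treatment they choose and in how they rate the consultation. If so, part of any pre-versus-active difference in survey outcomes would reflect who was counted rather than the intervention. Site and clinician effects cannot absorb this, because the imbalance follows phase within each site and clinician. A larger sample does not reduce it.

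A second, separate matter concerns reach. A woman first seen in the pre-implementation or initiation phase who is given the tool in the active phase appears in that phase's weekly count. The patient-level rule places her in the pre-implementation phase, or in neither compared phase.

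**Working it through.** The protocol states no figure for this point, so there is none to reproduce.

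**Step 1: look-back.** Let t be months since the start of the site's pre-implementation phase, and suppose the project period starts there. A first encounter at t means no visit for t months.

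- Pre-implementation: t runs from 0 to 6, mean 3.
- Active: t runs from 6 + 2 = 8 to 8 + 6 = 14, mean 11.

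If the project period instead began s months before the site's pre-implementation phase (a common start date), the ranges become s to s + 6 and s + 8 to s + 14. The gap is still 8 months, but it matters less as s grows.

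**Step 2: case mix.** The protocol gives no return-visit rate, so it is assumed. In a simulation, new patients present at a constant rate, each visit is followed by another with probability r, and the gap is exponential with mean 3 or 6 months. *New* means that the assigned encounter is the patient's first ever at the clinic. Each pair below is for mean gap 3 / 6 months.

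| r (assumed) | New, pre | New, active | Difference (points) | Seen in active phase but assigned elsewhere |
|---|---|---|---|---|
| 0.1 | 95.4% / 93.7% | 99.7% / 98.2% | 4.3 / 4.5 | 4.2% / 5.1% |
| 0.3 | 84.0% / 78.8% | 98.8% / 93.4% | 14.8 / 14.6 | 14.7% / 15.7% |
| 0.5 | 70.0% / 61.5% | 97.0% / 85.7% | 27.0 / 24.2 | 28.1% / 28.4% |
| 0.7 | 49.9% / 41.7% | 93.6% / 72.9% | 43.7 / 31.2 | 46.6% / 43.6% |

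**Step 3: bias in a survey outcome.** Bias = difference in case-mix share × difference in outcome between new and returning patients. Take the outcome difference as 5 to 15 points in top collaboRATE score (assumed).

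- r = 0.1: 0.043 × 5 = 0.2 to 0.045 × 15 = 0.7 points
- r = 0.3: 0.146 × 5 = 0.7 to 0.148 × 15 = 2.2 points
- r = 0.5: 0.242 × 5 = 1.2 to 0.270 × 15 = 4.1 points
- r = 0.7: 0.312 × 5 = 1.6 to 0.437 × 15 = 6.6 points

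The Power calculation section treats a margin of 0.048, or 4.8 points, as small. Among these values only the most extreme return rate, with a large outcome difference, passes it.

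**Step 4: does anything planned remove it?** The patient variables listed under Secondary outcome measures do not include new or returning status. The sensitivity analyses address dependence between repeat visits in the pre-implementation and active periods. They do not address who enters each phase, and they omit patients first seen during initiation.

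**Step 5: reach.** The last column of the table is the share of patients seen in the active phase whom the two rules place differently. The protocol does not say which rule governs their receipt.

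**The case against.** The rule has good reasons behind it. One phase per patient keeps the same woman out of both groups, and it avoids active-phase index visits that follow an earlier consultation and survey. The protocol foresees repeat visits, records them and adjusts for patient characteristics. A separate analysis plan could list prior-visit status among the covariates. Recurrent symptoms are not the same as a return visit: a woman with recurrence may be new to the clinic, and an established patient not seeking treatment is ineligible. Every size above is assumed.

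Most of this stands, and it limits the point. It does not remove the unequal look-back, which follows from a rule and phase lengths that the article itself states.

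Three stronger readings are tempting and should not be drawn:

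- **That active-phase receipt is charged to the pre-implementation phase.** The rule assigns patients; it does not say that later receipt is credited back. If only the first encounter counts, pre-implementation receipt stays at zero and later receipts are simply left out.
- **That the reach numerator and denominator follow different rules.** The Primary outcome measure section keeps both in one weekly log, and nothing limits that denominator to first encounters.
- **That the pre-implementation phase has no look-back at all.** It grows from 0 to 6 months within the phase. Even the zero depends on *project period*, which is undefined; with a common start date, later sites would have some.

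**Conclusion.** The point holds for the survey outcomes. If the project period starts with each site's pre-implementation phase, look-back is 8 to 14 months in the active phase against 0 to 6 before it, and the primary analysis does nothing stated to offset this. The likely result is a case-mix difference within site. For collaboRATE it amounts to about 0.2 to 0.7 points if returns are rare (r = 0.1) and 1.2 to 4.1 points at r = 0.5, given the assumed 5 to 15 point outcome difference.

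The pre-versus-active contrast in Option Grid receipt is largely protected, because the tool is not used before initiation and receipt there is zero whatever the case mix. For reach the defect is one of definition: the patient-level rule and the weekly count can place the same receipt differently, and the protocol does not say which prevails. This should be settled before analysis; it does not undermine the design.

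**What to change.** One phase per patient can be kept. The changes are:

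1. Define the project period for each site, starting with its own pre-implementation phase.
2. Equalise the look-back. Require no encounter at the site in the 8 months before the phase opens, read from the scheduling system. The active phase already implies this; applied to the pre-implementation phase it gives 8 to 14 months in both. Alternatively, adjust the primary models for prior-visit (new or returning) status. Adjustment leans more on the model, because the active group will hold few returning patients.
3. For reach, count every eligible patient seen in the active phase once, by encounter date, in both numerator and denominator.
4. Report an analysis by encounter date, with patient-level correlation, as a sensitivity analysis.

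The cost is a scheduling-system look-up, in a system the sites already consult, and a smaller pre-implementation sample if look-back is used as a restriction. In the simulation the active group was 0.94 to 0.95 times the size of the pre-implementation group at r = 0.1, 0.84 to 0.85 at r = 0.3 and 0.71 to 0.72 at r = 0.5. With a constant flow of patients, equal look-back would bring the pre-implementation group down to about the same size, a loss of roughly 5% to 29% over that range.

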### Data management and storage

All patient and clinician survey data will be stored in the Dartmouth Qualtrics database, a HIPAA-compliant web-based data management system. We will assign a unique study identification number to patient and clinician participants. All audio-recordings of clinical encounters and semi-structured interviews will be loaded by site-based project staff into Dartmouth’s HIPAA-compliant SharePoint system. Each recording will be labeled with a unique identification number. For statistical analysis, data will be downloaded from Qualtrics and stored on an encrypted hard drive owned by Dartmouth College. Stata software will be used for statistical analysis.

## Discussion

Our study maps the various routes to implementing PDAs in clinic workflow by studying timing and mode of delivery, available formats (online, text, and picture), and tailored implementation strategies determined by each organization’s readiness for patient engagement. This study also explores ways to overcome the barriers and facilitators to implementation from various stakeholder perspectives, guided by CFIR and NPT. Further, we will assess the impact of the implementation strategy on clinical and other relevant outcomes for women across socioeconomic strata. Our study aims to improve healthcare delivery for women with symptomatic uterine fibroids by empowering them, through the use of a PDA, to be more active in the decision-making process.

We anticipate that healthcare organizations who wish to use PDAs will use our findings to inform their implementation strategy. This work will help stakeholders identify *how* and *when* to best deliver these tools to patients. This study can help identify barriers to implementation of PDAs, enabling providers to proactively address such barriers. Reflecting on their workflow will enable site staff to understand how to potentially change their system to better identify eligible patients and deliver the tool in a minimally disruptive fashion. Findings can encourage clinicians in gynecology departments to use PDAs with their patients given the positive effects of these tools on communication and outcomes.

The use of two validated frameworks to guide each site’s implementation strategy is a strength of our study [21–24]. In addition, we are assessing implementation from various stakeholder perspectives using both qualitative (interviews) and quantitative (survey) methods. We are providing each site with flexibility, so they can determine how best to implement Option Grid based on their clinic workflow patterns and organizational readiness for this type of approach. A potential limitation is that the outer setting domain of the CFIR framework is not addressed as extensively as the other domains (see Table 1). However, the integration of new evidence into existing clinical practice guidelines (component 4 of our strategy) addresses, to an extent, the external policy and incentives construct embedded in the CFIR outer setting domain. A further challenge will be determining the best method to ensure that all eligible patients receive the uterine fibroid Option Grid. However, we are collaborating with principal investigators, who are all practicing clinicians, at each site to overcome this challenge.

We will take an active approach to disseminating study findings by engaging key stakeholders—patients, caregivers, community members, health professionals, and policy makers—in identifying the message and the means of communication to appropriate audiences [42]. Potential dissemination strategies may include the use of social media, lay press, and academic.

## Data Availability

Data sharing is not applicable to this article as no datasets were generated or analyzed during the current study.

## Abbreviations

CBPR: Community-based participatory research
CFIR: Consolidated Framework for Implementation Research
COST: The Comprehensive Score for financial Toxicity
NPT: Normalization Process Theory
PDAs: Patient decision aids
UFS-QOL: Uterine Fibroid Symptom and Health-Related Quality of Life Questionnaire
